**Outcomes**

The main outcomes in this aim include the binary variable tax awareness and the latent variables SSB knowledge and SSB risk perception, which we will measure with confirmatory factor analysis.

**Confirmatory Factor Analysis Variable Construction**

Measurement tools for participants’ SSB knowledge and SSB risk perceptions are described in “Measures and Data Collection” above (p. 9). Responses to SSB knowledge and SSB risk perception questions will be used to develop two distinct composite measures for our SSB knowledge score using confirmatory factor analysis performed in MPlus.

Confirmatory factor analysis is a method for establishing the validity of using a set of observations for measuring a latent variable. A set of survey questions is typically developed because there is a theoretical variable that explains the responses to observable variables. For example, the condition of having depression might explain a person’s responses to a mood questionnaire, even if depression itself is not directly observable. One approach to measuring depression might be to sum or average the scores on depression-related questions. However, each observable survey question has considerable measurement error, the magnitude of which will be unequal for each question^88^. Such cases benefit from using statistical models like confirmatory factor analysis that can reduce this measurement error, and using multiple indicators of a construct contains more information than any survey question individually. In our case of measuring responses to SSB knowledge and risk perception questions, any single question identifying a certain is better understood as a composite measure of all the answers than using the questions individually. Also, given that our survey questions on SSB knowledge and SSB risk perception are expected to be answered similarly according to participants’ true underlying knowledge and risk perception, including all of these variables separately in a regression model would introduce problems of variable multicollinearity.

Therefore, we will conduct a confirmatory factor analysis because this statistical technique accounts for differences in measurement error between each of the questions used to measure the latent variables SSB knowledge and SSB risk perception. Preliminary results from confirmatory factor analysis using baseline data suggest that our survey questions are effectively measuring the latent variables of SSB knowledge and risk perception according to overall model fit, R squared values for each observed variable (the survey questions), and statistically significant factor loadings. Chi-square fit statistics are not appropriate for this study as it is highly influenced by sample size, with larger samples (>400 observations) making it more likely to have a statistically significant model fit^89^. Instead, we will use the Comparative Fit Index (CFI), as it is less sensitive to sample size. A value of at least 0.90 is considered a good model fit^90^, and according to results generated in MPlus using our baseline data, the CFI is 0.972 for SSB knowledge and 0.999 for risk perception, both indicating excellent model fit^90^. The Root Mean Squared Error of Approximation measures closeness of fit, and our baseline RMSEA is 0.034 for SSB knowledge and 0.014 for risk perception, both meeting the <0.05 criterion for good model fit^90,91^. We will repeat the model fit testing at each time point separately to ensure the models fit the data sufficiently well, and we will perform a series of configural invariance tests for each separate time period to test whether the same CFA is valid in each group. These tests ensure that factor loadings and intercepts are the same across groups and the responses are therefore comparable.

After the confirmatory factor analysis, we will first test whether our potential modifiers change significantly over time. This will be done by setting our latent variable—for SSB knowledge and then for risk perception—as a continuous dependent variable in a linear regression model and entering time (coded 0, 1, 2 for baseline, 6 and 12 months, respectively) as the independent variable. The coefficient for time will indicate the change in knowledge (or risk perception) for a unit change in time period, and the p value will indicate whether this result is statistically significant. For the binary variable tax awareness (yes/no), we will measure change over time using two sample t-tests, comparing the mean awareness at 6 months to baseline and 12 months to baseline.

Next, we will determine whether SSB knowledge, SSB risk perception, or tax awareness modify the relationship between time and taxed beverage consumption. Using linear regression models, we will test whether the relationship between our potential modifiers and taxed SSB consumption differs by time using interaction terms. We will test for interaction with a Wald test. We will conduct a pooled analysis using all observations from baseline, 6 months, and 12 months post-tax when testing these models, with dummy variables coded 0, 1, 2 to indicate each data collection time period. Our potential modifiers of SSB knowledge and risk perception will be kept as continuous variables because categorization results in a loss of information, and there is no substantive reason for creating arbitrary cutoffs when testing this interaction. Models will be controlled for individual level covariates listed in Table 4, weekday of interview, and temperature (to control for seasonality).

**Expected Results:** In accordance with our conceptual model, we expect to see tax awareness, SSB knowledge, and SSB risk perception to increase over time. We expect a significant interaction between time of data collection and SSB knowledge score, such that a higher knowledge about health risks will be associated with lower SSB intake, and this relationship will be stronger after the tax. This would suggest that knowledge is a statistically significant modifier of the change in SSB consumption after the tax in our sample. We expect to see similar effect modification for risk perception. For tax awareness, we expect there to be a statistically significant increase at 12 months given that participants will have noticed increased prices of SSBs in shops. We expect a significantly lower taxed beverage intake among those who are aware of the SSB tax at 12 months compared to those who are unaware. It is possible that there is no difference in awareness at 12 months after the tax compared to baseline, recorded the month before the tax was implemented. This result would suggest that media coverage of the tax has not penetrated into the Langa township, and will provide some explanation for the possibility of finding a small amount of change in Aim 1.

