**Table 4. Outcomes and Covariate measures for model adjustment**

| **Primary outcomes** |  |
| --- | --- |
| Taxed beverage volume | Taxed based on having more than 4g of sugar per 100ml |
| Taxed beverage calories |  |
| **Secondary outcomes** |  |
| Untaxed beverage volume | Untaxed based on having less than 4g of sugar per 100ml |
| Untaxed beverage calories |  |
| **Potential modifiers** |  |
| SSB knowledge | Latent variable obtained from confirmatory factor analysis (CFA), for knowledge of whether selected beverages contain added sugars. |
| SSB risk perception | Latent variable obtained from confirmatory factor analysis (CFA), for perceived risk of NCDs due to SSB consumption |
| **Covariates** |  |
| Individual-level covariates | Age (continuous, range 18-39), sex, total energy intake, BMI, smoking (yes/no), alcohol intake, socioeconomic status (ordinal categorical), disease status (diagnosis of diabetes, heart disease, high cholesterol, high blood pressure, cancer, or obesity) |
| Weekday | Diet intake reported for weekday versus weekend (binary) |
| Temperature | Obtained from South African Weather Service, to control for seasonal changes in SSB intake |
| Time period | Categorical: 0 (baseline), 1 (6 months), 2 (12 months) |

**Expected Results:** Based on results from Mexico and Chile where an SSB tax was implemented, we hypothesize that taxed SSB consumption by 18-39 year-olds living in Langa will decrease by 6% at 12 months. Based on the magnitude of change reported from previous SSB tax evaluations, we do not expect to have sufficient power to detect a statistically significant change in taxed SSB consumption by 6 months.

*Analysis of taxed/untaxed beverage subcategories*

We will repeat the above analysis for beverage subcategories (Table 3), using both approaches for linking FCT data to dietary intake data to account for potential reformulation across beverage subcategories.

*Comparison of diet assessment methods*

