**Aim 2:** **Examine changes in tax awareness, SSB knowledge, and SSB risk perception, and determine whether these variables modify the relationship between SSB consumption and time since tax implementation.** The key goal for Aim 2 is to test whether tax awareness, knowledge, or risk perception change over time after tax implementation and whether these variables modify the relationship between SSB consumption and time since tax implementation. We will test (1) whether there are significant differences in mean SSB knowledge, risk perception and prevalence of tax awareness before and after the tax (2) whether there is a time*modifier interaction on taxed SSB intake, pooling data from baseline, 6, and 12 months. Aim 2 will be completed using the same study population as Aim 1. The rationale for this analysis is depicted in Figure 4, where SSB knowledge score modifies the relationship between SSB tax implementation and SSB consumption.

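### Aim 2 credits configural invariance tests with establishing equal loadings and intercepts, and its change models for knowledge and risk perception use one linear time slope although Table 4 defines time as categorical

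*Protocol*

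**What the plan says.** Under Confirmatory Factor Analysis Variable Construction (Aim 2), the protocol first checks fit wave by wave: "We will repeat the model fit testing at each time point separately to ensure the models fit the data sufficiently well". It continues: "we will perform a series of configural invariance tests for each separate time period to test whether the same CFA is valid in each group". The next sentence states what this achieves: "These tests ensure that factor loadings and intercepts are the same across groups and the responses are therefore comparable". Metric and scalar invariance are not named.

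The opening paragraph of Aim 2 gives the first question as "whether there are significant differences in mean SSB knowledge, risk perception and prevalence of tax awareness before and after the tax", and the Outcomes paragraph lists tax awareness and the two latent variables as the main outcomes of the aim.

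Time is handled in four ways:

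- Table 4, time period: "Categorical: 0 (baseline), 1 (6 months), 2 (12 months".
- Change models for knowledge and risk perception: "entering time (coded 0, 1, 2 for baseline, 6 and 12 months, respectively) as the independent variable", with the reading "The coefficient for time will indicate the change in knowledge (or risk perception) for a unit change in time period".
- Change in tax awareness: two-sample t tests of 6 months against baseline and of 12 months against baseline.
- Interaction models: the time terms are called dummy variables but given the values 0, 1 and 2; the interaction is tested with a Wald test.

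**The concern.** A difference in latent means between waves can be read as a change in knowledge or risk perception only if the items relate to the factor in the same way at each wave, in both loading and intercept. A configural model leaves loadings and intercepts free, so passing it says nothing about either. An analyst who follows the named test stops before the condition that the protocol itself relies on has been examined. A change in how one or two questions are answered after the tax publicity could then be taken for a change in the underlying trait. The modifier analysis is also touched: comparing the slope of intake on a latent modifier across waves needs at least equal loadings.

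The time coding matters because a single slope forces the 0-6 and 6-12 month changes to be equal and cannot show a rise that fades. Such a pattern is plausible on the protocol's own reasoning. The Expected Results of Aim 3 place the peak of press coverage in April 2018, and the Methods overview routes part of the media effect through consumer knowledge.

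**Working it through.** The protocol states no figure on this point, so there is none to reproduce.

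**Invariance.** Set the named test beside the claimed result:

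| Level | What is held equal across waves | What it supports |
|---|---|---|
| Configural (named) | pattern of items on factors | same structure |
| Metric (not named) | plus loadings | comparing regressions on the factor |
| Scalar (not named) | plus intercepts or thresholds | comparing latent means |

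The claimed result is the second and third rows; the named test is the first. Fit judged separately at each wave cannot fill the gap, because an intercept shift leaves the item covariances unchanged and so does not move CFI or RMSEA.

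As an illustration, take a one-factor model with five standardised items (the protocol lists five risk conditions). Assume a loading of 0.7, no true latent change and 2,383 per wave. The loading, the shift and the later wave sizes are assumptions.

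- Residual variance: 1 - 0.7² = 0.51. Sum of λ²/ψ: 5 × 0.49/0.51 = 4.804.
- Regression-score weight per item: (0.7/0.51)/(1 + 4.804) = 0.236.
- SD of the score: √(4.804/5.804) = 0.910. SE of a wave difference in SD units: √(2/2383) = 0.029.
- One item shifted by 0.2 SD: 0.2 × 0.236 = 0.047 latent SD, z about 1.8.
- Two items shifted by 0.2 SD: 0.095 latent SD, z about 3.6.

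**Time coding.** The least-squares slope is a weighted sum of the wave means with weights n_k(t_k - t̄)/Σn_k(t_k - t̄)², where t = 0, 1, 2. Only the baseline size of 2,383 is given, so a range is shown:

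| Wave sizes (0, 6, 12 months) | Weights |
|---|---|
| 2383, 2383, 2383 | -0.500, 0.000, 0.500 |
| 2383, 1200, 2383 | -0.500, 0.000, 0.500 |
| 2383, 2500, 2500 | -0.496, -0.008, 0.504 |
| 2383, 2000, 1800 | -0.523, 0.046, 0.477 |
| 2383, 2383, 1500 | -0.545, 0.089, 0.455 |
| 2383, 2383, 1200 | -0.571, 0.141, 0.429 |

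With equal waves the slope is half the baseline-to-12-month difference.

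Power at two-sided 0.05, SD 1 and 2,383 per wave: the slope has SE 1/√(2 × 2383) = 0.0145; the 2-df test has noncentrality 2383 × Σ(m - m̄)².

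| Wave means (SD) | Slope | Power, slope | Power, 2 df |
|---|---|---|---|
| 0, 0.10, 0 | 0.000 | 0.050 | 0.955 |
| 0, 0.10, 0.05 | 0.025 | 0.408 | 0.881 |
| 0, 0.10, 0.10 | 0.050 | 0.932 | 0.955 |
| 0, 0.05, 0.10 | 0.050 | 0.932 | 0.881 |

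In the second row the slope implies a 6-month change of 0.025 SD where the true one is 0.10.

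**The case against.** On invariance, the best reply is that this is a mislabel. The plan speaks of a series of tests and states the right target, equal loadings and intercepts, so the authors may well have meant the full sequence. That stands as to intent. It does not make the sentence correct, and an analyst working from the named test would stop too early.

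On time coding, the Expected Results of Aim 2 predict a rise over time, and a linear score suits that prediction; under a truly linear trend it is the more powerful test. That also stands, but it does not settle the conflict with Table 4.

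A reader might be tempted to go further in four ways that the document does not support:

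- **That the 6-month wave is ignored.** Its data are in the model and contribute to the residual variance. Its mean has zero weight only when the baseline and 12-month waves are equal in size, and tax awareness has its own 6-month contrast.
- **That the interaction models also fit a linear time score.** Dummy variables, interaction terms in the plural and a Wald test read naturally as a three-level factor. Only the description of the coding is loose.
- **That no latent mean change could be estimated, because a configural model usually fixes each wave's factor mean at zero.** This would depend on how the latent variable is carried into the regression on time, which the protocol does not say. Nor can it hold of the same model in which item drift appears as a mean change.
- **That leaving covariates out of the change models contradicts the protocol.** Table 4 does not require adjustment at that step, Aim 1 also reports unadjusted results, and the sentence on covariate control is not expressly limited to the interaction models.

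**Conclusion.** Two corrections are warranted. First, the statement about what configural tests establish is wrong, and the comparison of mean knowledge and risk perception across waves depends on the scalar invariance that it leaves unnamed. Whether invariance fails in these data is unknown. The illustrated bias of 0.047 to 0.095 latent SD rests on assumed loadings, item shifts and wave sizes, and shows that the matter can count, not that it does.

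Second, the single slope for the two latent outcomes is at odds with Table 4 and with the treatment of tax awareness, and it cannot show a non-monotone change. The extreme loss, power 0.05 against about 0.96, belongs to a change that has fully reversed by 12 months with equal waves. If the change is sustained at 12 months, the slope loses little or nothing.

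Both are inexpensive to correct and neither affects Aim 1. They should be settled before the Aim 2 analysis is run.

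**What to change.** 1. Replace the reference to configural tests with a multi-group analysis by wave, in the order configural, metric, scalar (thresholds for the ordinal items), judged by the change in CFI and RMSEA. State that latent means are compared only under full or partial scalar invariance.
2. In the change models for knowledge and risk perception, enter time as two indicators, 6 months and 12 months against baseline, in line with Table 4 and the tax awareness contrasts.
3. In the interaction models, describe the time terms as two indicators and the test as a 2-df Wald test.

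As a secondary suggestion, say whether the change models are adjusted for age, sex and socioeconomic status, since each wave is a separate cross-section.

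The cost is a few more model runs, some rewording and one extra degree of freedom. If the trend is truly linear and reaches 0.10 SD at 12 months, power falls from about 0.93 to about 0.88, assuming 2,383 per wave.

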Linear regression models will be used to estimate taxed and untaxed beverage consumption at each time point, adjusted for the covariates listed in Table 4. We will estimate unadjusted results, adjusted results (including individual level-covariates, weekday of intake, and temperature), and finally results adjusted for these covariates plus BMI. These models will include adjustment for total energy when using 24-h recall data. Given that our FFQ cannot be used to obtain total energy intake, adjusting for BMI will allow us to potentially control for variation in total energy intake in our sample. Comparisons between baseline and 6 month and between baseline and 12 month means will be made with two-tailed t tests. We plan to use both the 24-h recall and the FFQ for these analyses. For the FFQ, we will multiply the amount reported as most commonly consumed times a frequency per day (e.g. intake amount of once per week would be multiplied by 1/7) to obtain daily intake.

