**Limitations**

*Study design*

Given that our data are cross-sectional and not longitudinal, we are not able to follow individuals over time, only measure differences in population means. Social desirability bias could affect reporting of SSB intake and cause us to underestimate SSB intake. It is also possible that after the tax, social norms may have shifted so that the effect of social desirability bias is even greater after SSBs are subject to tax, causing an overestimation of reductions in SSB intake in this population.

*Repeated individuals across data collection periods*

We are using a repeated cross-sectional study design, and it is possible that we have repeated individuals surveyed at more than one time point. We do have a variable that indicates whether participants were included in our sample at previous data collection points, but the individual identifiers were generated using a method that does not allow for individuals to be linked across time. This limitation could potentially bias our results by an unknown magnitude and direction, given that we cannot know whether repeated individuals were high or low consumers of a given beverage category.

*Accuracy of FCT beverage codes*

Although the beverage codes that we are developing for our UNC-UWC FCT are based on nutrition information of South African beverages, they still represent an average and therefore it is possible that some beverages may be misclassified as taxed or untaxed if the actual products consumed differ in their sugar content to the average sugar content calculated for the beverage category. For example, if there is brand-specific reformulation, where some soda brands reduce their sugar (to become untaxed) and others do not (remain taxed), this could lead to misclassification. The potential for misclassification of beverages is even greater for the FFQ versus the 24-h recall because the beverage categories reported are broader than the individual beverage codes contained within each beverage subcategory.

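### Aim 2 tests change in tax awareness with raw t-tests and names no covariate but time for knowledge and risk perception, so a difference in sample mix between waves would be read as change after the tax

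*Protocol*

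**What the plan says.** The opening paragraph of Aim 2 sets as its first test "whether there are significant differences in mean SSB knowledge, risk perception and prevalence of tax awareness before and after the tax". The methods come after the description of the confirmatory factor analysis:

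- **Knowledge and risk perception.** Each latent score is set "as a continuous dependent variable in a linear regression model and entering time (coded 0, 1, 2 for baseline, 6 and 12 months, respectively"). No other regressor is named.
- **Tax awareness.** The plan states: "For the binary variable tax awareness (yes/no), we will measure change over time using two sample t-tests". The 6-month and 12-month waves are each compared with baseline.
- **Interaction models.** The next paragraph turns to effect modification of taxed beverage intake and ends: "Models will be controlled for individual level covariates listed in Table 4, weekday of interview, and temperature (to control for seasonality"). This is the only covariate sentence in the Aim 2 methods.

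In the Aim 1 Analysis Plan, beverage intake at each time point is "adjusted for the covariates listed in Table 4", with unadjusted results also reported.

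On design, the Aim 1 limitations say: "Given that our data are cross-sectional and not longitudinal, we are not able to follow individuals over time, only measure differences in population means". The same section allows that some people may have been surveyed at more than one wave, without a way to link them.

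**The concern.** When different people are interviewed at each wave, a raw difference between waves has two parts: change in the population, and any difference in who was interviewed. The plan adjusts for personal characteristics in two of its three analyses of these data, but its stated method for this one does not.

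The result also carries weight. Under Expected Results for Aim 2, a rise in awareness is attributed to people noticing higher prices. No rise is taken to mean that media coverage did not reach the township, and is offered as a partial explanation for a small Aim 1 effect. A difference in sample mix could produce or hide either finding. The Aim 2 limitations mention that individuals are not tracked and that social desirability may act, but not a shift in sample composition.

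**Working it through.** The protocol gives no figure for these tests, so there is nothing to reproduce. The check is a reading of the text, followed by an illustration of size.

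**Reading**

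1. Awareness: a two-sample t-test has no place for covariates. The method as fixed is unadjusted.
2. Latent scores: time is the only regressor named. The covariate sentence closes a separate paragraph about models with taxed intake as the outcome. On the plain reading it does not reach back to the score regressions, but the text does not rule covariates out either.
3. Sampling: the Langa 18-39y Survey recruited door to door, with age as the only eligibility criterion. No quota or weighting is described that would hold the mix constant across waves.

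**Illustration: latent score**

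Inputs:
- n = 2,383 per wave. This is the baseline size; the sizes at 6 and 12 months are not stated, so equality is assumed.
- Two-sided 5% level, assumed. The protocol sets no level for Aim 2; the only one it states is 0.1, under Study Power.
- No true change; a subgroup difference of 0.3 SD; a shift in subgroup share of 5 or 10 percentage points. All are assumed.

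Formulas:
- Spurious change = subgroup difference × shift in share
- SE of a standardised difference between two waves = √(2/n) = √(2/2383) = 0.029
- z = spurious change / SE
- Rejection probability = 1 − Φ(1.96 − z) + Φ(−1.96 − z)

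| Shift | Spurious change | z | Rejection probability |
|---|---|---|---|
| 5 points | 0.3 × 0.05 = 0.015 SD | 0.52 | 0.075 + 0.007 = 0.081 (before rounding of the terms) |
| 10 points | 0.3 × 0.10 = 0.030 SD | 1.04 | 0.178 + 0.001 = 0.179 |

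The three-wave linear trend gives the same z if the shift is even across waves. The slope is half the spurious change and its SE is √(1/(2n)), so z = (change/2) × √(2n) = change / √(2/n).

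Over subgroup differences of 0.2 to 0.5 SD and shifts of 5 to 15 points, the spurious change is 0.01 to 0.075 SD and the rejection probability about 6% to 74%.

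**Illustration: awareness**

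Assume 30% aware at baseline, a 20-point difference in awareness between subgroups, and the same n and level.
- SE = √(2 × 0.3 × 0.7 / 2383) = 0.0133
- 5-point shift: spurious change 0.20 × 0.05 = 1 point, z = 0.75, rejection about 12%
- 10-point shift: spurious change 0.20 × 0.10 = 2 points, z = 1.51, rejection about 33%

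Over awareness of 20% to 50%, subgroup differences of 10 to 30 points and shifts of 5 to 15 points, the rejection probability runs from about 6% to 97%. A range this wide shows how far the result depends on inputs that the protocol does not give.

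**The case against.** Several objections have force.

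- **No shift is shown.** A reader might infer that composition did change, perhaps because the baseline sample was 65% female (Table 2) while the township is 50.4% female. That does not follow. The comparison sets one wave against residents of all ages. It suggests selection at baseline, and the same selection repeated at each wave would not bias the change. One recruitment method and one age criterion are described throughout. This objection stands, and it limits the point to what would happen if the mix differed.
- **The latent-score models are not declared unadjusted.** A reader might infer that the plan excludes covariates there. It only fails to name them, and Table 4 lists covariates for model adjustment in general. Only for awareness does the stated method rule adjustment out.
- **The contrast with Aim 1 is not a contradiction.** The protocol never says it adjusts because the waves are cross-sections. The reasons it gives are season for temperature and energy intake for BMI, and both concern beverage intake. What remains is a difference in treatment that is not explained.
- **The waves may overlap.** It is too strong to treat every wave as entirely new people. The Aim 2 limitations do speak of new individuals, but the Aim 1 limitations allow for repeats. Overlap might dampen a shift in mix; it does not rule one out.
- **The target is descriptive.** Raw differences do estimate the difference between the groups sampled, and the protocol disclaims causal conclusions for Aim 2. This mitigates the problem without curing it, because Expected Results interprets the awareness change in substantive terms.

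**Conclusion.** The point holds in a limited form. The stated test for awareness cannot be adjusted, and no covariate besides time is named for the two latent-score change models. The design does not guarantee the same mix of people at each wave. Any difference in age, sex or socioeconomic mix would therefore be read as change after the tax.

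How much this matters is unknown. The 8% to 18% false-positive rate for a latent score, against a nominal 5%, rests on assumed wave sizes, an assumed level, a 0.3 SD subgroup difference and a 5- to 10-point shift. None of these is established for the 6- and 12-month waves, and the spurious change involved is at most 0.03 SD. The documents do not support saying that the Aim 2 change results will be biased. They support saying that the plan leaves out a cheap safeguard that it uses elsewhere.

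**What to change.** 1. Replace the awareness t-tests with a regression of awareness on wave, entered as categorical, plus age, sex and socioeconomic status from Table 4. Report adjusted prevalence differences at 6 and 12 months against baseline.
2. State the same covariates in the knowledge and risk-perception change models.
3. Keep the unadjusted results alongside, as Aim 1 does.
4. Add to the Aim 2 limitations that adjustment removes only measured differences in composition.

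The cost is wording and a few extra model fits. The socioeconomic measures are stated to be collected at all three waves. That age and sex are available at each wave is implied by the adjusted models already planned, and should be confirmed.
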